## Abstract

**Background:**

The ability of a preventive nutritional intervention to reduce the morbidity of gestational diabetes mellitus (GDM) remains controversial. We aim to assess whether GDM can be prevented by an individualised nutritional intervention in pregnant women who are at high risk for the disease based on a prediction model.

**Methods/design:**

A multicentre randomised controlled trial was designed to assess the efficacy of an individualised nutritional intervention for the prevention of GDM in a high-risk population screened by a novel prediction model in the first trimester. Pregnant women evaluated to be at high risk for GDM by the prediction model at less than 14 gestational weeks will be included. Women with pre-existing chronic diseases, including pregestational diabetes, or who are currently prescribed medicines that affect glucose values will be excluded. Allocation to intervention/control at a ratio of 1:1 will be conducted by a computerized randomisation system. The intervention group will complete 3-day food records and receive 3 individualised nutritional consultations with professional dieticians before the oral glucose tolerance test. The primary intention of the intervention is to promote a long-term healthy dietary pattern and prevent excessive gestational weight gain throughout pregnancy. The control group will complete 3-day food records at designated gestational weeks and receive standard antenatal care according to local health care provisions. The primary outcome is the incidence of GDM according to the criteria of the International Association of Diabetes and Pregnancy Study Group (IADPSG). A sample of 464 participants will provide 80% power to detect a 30% reduction in GDM incidence (α = 0.05 two tailed, 10% dropout). A total of 500 participants will be recruited.

**Discussion:**

To date, this is the first randomised controlled trial aimed to evaluate the protective effect of an individualised nutritional intervention against GDM based on a logistic regression prediction model. Eligibility is not limited to obese women or singleton pregnancies, as in previous studies. This pragmatic trial is expected to provide valuable information on early screening and effective GDM prevention methods.

**Trial registration number:**

ChiCTR, ChiCTR1900026963. Registered 27 October 2019.

**Supplementary Information:**

The online version contains supplementary material available at 10.1186/s12884-021-04039-2.

## Background

Gestational diabetes mellitus (GDM) is a common, pregnancy-specific disorder diagnosed at 24–28 gestational weeks. The East Asian population has high GDM susceptibility, with an incidence rate of 11.7% (range: 4.5–25.1%) [1]. The current diagnostic criteria for GDM are inconsistent worldwide. The international medical community, including that in China, adopts the results of the 75 g oral glucose tolerance test (OGTT) at 24–28 gestational weeks as diagnostic criteria as recommended by the IADPSG and the American Diabetes Association (ADA) (fasting venous glucose ≥5.1 mmol/L, 1-h value ≥10.0 mmol/L, 2-h value ≥8.5 mmol/L) [2, 3]. GDM can exert several adverse effects in both mothers and children, including polyhydramnios, macrosomia and neonatal hypoglycaemia [4, 5]. Moreover, reasonable evidence has indicated that exposure to an intrauterine hyperglycaemic environment leads to an increased risk of chronic health issues in filial generations, such as cardiovascular diseases, diabetes mellitus, and obesity [6–8]. Despite the adverse effects of GDM, referral to professional nutritionists for individualised lifestyle modifications before the OGTT is infrequently implemented in current clinical practice in China.

Previous studies have indicated that lifestyle modification strategies addressing healthy eating and/or physical activity can effectively prevent type 2 diabetes mellitus in nonpregnant populations [9]. Nutritional patterns in early pregnancy have been suggested to be associated with GDM development [10]. Counselling and behavioural interventions have been reported to be effective in limiting excess gestational weight gain (GWG), which is associated with a decreased risk of GDM [11–13]. As a first-line strategy for GDM management, nutritional interventions mainly involve a dietician’s personalised diet prescription in accordance with nutritional intake guidelines during pregnancy [14]. A prospective study with a small sample size (*n* = 50) suggested that GWG in obese women (body mass index (BMI) ≥ 30 kg/m^2^) can be reduced through the implementation of 10-h dietary consultations (gain of 6.6 kg in the intervention group vs gain of 13.3 kg in the control group, *p* = 0.002), thus reducing the incidence of GDM (0% in the intervention group vs 10% in the control group) [15]. The conclusions of an RCT conducted in nine European countries with 150 participants with BMI ≥ 29 kg/m^2^ support the application of early healthy eating interventions in obese pregnant women, as evidenced by lower GWG and lower fasting glucose in the intervention group [16]. Another prospective randomised controlled trial with a larger sample size (*n* = 269) conducted in Finland showed that obese pregnant women (BMI ≥ 30 kg/m^2^) who received individualised counselling on physical activity, diet, and weight gain control from trained nurses and dieticians had a lower prevalence of GDM (13.9% in the intervention group vs 21.6% in the control group, *p* = 0.044) [17]. Nevertheless, the UPBEAT study from the UK indicated that behavioural intervention in obese pregnant women (BMI ≥ 30 kg/m^2^) was not adequate to prevent GDM (25.0% in the intervention group vs 26.0% in the standard care group, *p* = 0.68) [18]. Currently, the level of evidence on whether nutritional intervention can prevent GDM is considered to be low to very low since it is challenging to implement these interventions and monitor measurement error and diet complexity under free-living circumstances [19, 20]. On the other hand, previous studies mostly targeted obese pregnant women with singleton pregnancies or those with a previous history of GDM [14, 15, 17]. As stated in a study conducted in America, nearly one-third of GDM patients (29.3%) were underweight or normal weight [21]. Currently, it remains unproven whether nutritional intervention can prevent GDM in a more general population, such as normal-weight women, women with multiple pregnancies or women with fasting blood glucose equal to or higher than 5.1 mmol/L in the early conception period. Therefore, modifiable risk factors and pragmatic interventions need to be identified.

Given the promising potential to relieve the social and economic burden of GDM, comprehensive and high-quality clinical research with adequate power to identify evidence-based preventive strategies is urgently warranted. Therefore, we present a multicentre, open-label and parallel-group randomised study protocol to explore whether an individualised nutritional intervention can effectively reduce the prevalence of GDM in pregnant women who have been identified by a prediction model in the first trimester to be at high risk for the disease. Previous studies have built various risk evaluation models for GDM taking different clinical risk factors into consideration; however, these models lack external validation or applicability for clinical practice [22–24]. Prior to the design of this study, we developed a novel logistic regression prediction model via advanced machine learning, the establishment details of which have been published previously [25]. The model selected 7 out of 73 clinical indicators: age, blood triglyceride level, fasting blood glucose and HbA1c levels in early pregnancy, family history of diabetes in first-degree relatives, multiple pregnancy and previous history of GDM. These indicators were considered to be sensitive predictors of GDM as early as the initiation of pregnancy in previous studies [22–24, 26–30]. With a solid theoretical foundation, this pragmatic trial will provide reliable clinical evidence of the efficacy of an individualised nutritional intervention to prevent GDM among high-risk populations.

### Objective and hypothesis

The aim of this trial is to evaluate the effectiveness of an individualised nutritional intervention for the prevention of GDM among high-risk pregnant women screened by a novel risk prediction model in the first trimester. We hypothesise that providing individualised nutritional consultations at least once a month before the OGTT for high-risk pregnant women will reduce the prevalence of GDM and improve maternal and offspring perinatal outcomes.

## Methods and analysis

### Study design and setting

The proposed study is a multicentre, open-label, parallel-group randomised trial. A total of 500 eligible women will be recruited from 3 different tertiary hospitals, including +/− 300 from the International Peace Maternity and Child Health Hospital, +/− 100 from Xinhua Hospital, and +/− 100 from Shanghai Fengxian District Central Hospital. A flowchart of participant recruitment, randomisation and follow-up is shown in Fig. 1 (see Additional file 1).

**Fig. 1 Fig1:**
[figure not shown]
Flowchart of participant recruitment, randomisation and follow-up

### Participants

Women in early pregnancy who attend the antenatal clinics of three research centres will be identified by the GDM risk prediction model mentioned above. According to the multiple logistic regression model we previously established, the predictive probability of GDM development in our study population will be calculated with the formula 1/[1 + exp.(−β)], in which β equals (− 14.2334 + (0.0681*age) + (0.5005* blood triglyceride level in the first trimester, mmol/L) + (2.8165* fasting blood glucose level in the first trimester, mmol/L) + (1.1062*family history of diabetes in first-degree relatives) + (1.6925* HbA1c in the first trimester, %) + (0.4349*multiple pregnancy) + (2.6181* previous history of GDM). The area under the receiver operating characteristic curve of this model was 0.77 (95% CI 0.76–0.78). The optimum threshold probability was 0.13 with 59% sensitivity and 82% specificity when the Youden index was set at 0.41 [24]. Consequently, pregnant women with a calculated risk probability of GDM equal to or higher than 0.13 in the first trimester are considered high risk. Among them, pregnant women at less than 14 gestational weeks who are able to understand and provide informed consent and are ready to receive antenatal care and deliver at one of the research centres will be eligible to participate in our study.

We will exclude individuals if they have been diagnosed with the following disorders: pre-pregnancy essential hypertension, renal disease, HIV, hepatitis B or C, cardiac disease, thalassemia, cystic fibrosis, systemic lupus erythematosus or any other autoimmune disease, thyroid disease requiring medication, pregestational diabetes (including patients diagnosed with diabetes before conception; fasting blood glucose ≥7.0 mmol/L or HbA1c ≥ 6.5% in the first trimester; typical hyperglycaemic symptoms or hyperglycaemic crisis with optional blood glucose ≥11.1 mmol/L), or current prescription of medicines, such as metformin and glucocorticoids, that affect blood glucose values.

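### The printed GDM risk equation puts every plausible woman above the 0.13 eligibility threshold, so it cannot have the stated 82% specificity

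*Protocol article*

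**What the plan says.** The Participants section commits the trial to a specific calculation: "the predictive probability of GDM development in our study population will be calculated with the formula". The form given is the usual logistic one, 1/[1 + exp(−β)]. The section prints β in full, with an intercept of minus 14.2334 and seven terms. The intercept and age term read "14.2334 + (0.0681*age". Glucose enters as "2.8165* fasting blood glucose level in the first trimester, mmol/L", and the HbA1c term, in percentage points, is "1.6925* HbA1c in the first trimester". The other coefficients are 0.5005 per mmol/L of triglycerides, 1.1062 for a diabetic first-degree relative, 0.4349 for multiple pregnancy and 2.6181 for previous GDM.

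Performance is given next to the equation: "The optimum threshold probability was 0.13 with 59% sensitivity and 82% specificity", with a Youden index of 0.41. The eligibility rule follows: "pregnant women with a calculated risk probability of GDM equal to or higher than 0.13 in the first trimester are considered high risk".

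Three other parts of the article bear on this:

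- Participant timeline has recruiting staff apply the model to every woman at the antenatal clinics.
- Sample size calculation takes about 30% GDM incidence among women the model flags.
- Background gives an East Asian incidence of 11.7% (range 4.5–25.1%).

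**The concern.** Fasting glucose and HbA1c are always present and carry large positive coefficients. For ordinary values they alone add more than 20 to β, while the intercept subtracts only about 14. The result is a large positive β and a probability close to 1, whereas the threshold of 0.13 needs β near -1.9. An equation that scores everyone above the threshold cannot have 82% specificity there.

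This rule is the trial's only enrichment step. The objective, the trial population and the 30% planning incidence all depend on it. If the centres calculate eligibility from the printed equation, the trial enrols unselected women and no longer tests prevention in a high-risk group. Even if they do not, a reader cannot apply or check the eligibility rule from the article.

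**Working it through.** **Inputs.** Coefficients, units, link and threshold come from Participants. The incidence figures come from Background and Sample size calculation. The article gives no distribution of the covariates, so the profiles below are assumptions, chosen to run from ordinary to implausibly low. All have a single fetus, no family history and no previous GDM. Those three coefficients are positive, so any such factor would only raise the score.

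**Check of the stated performance.** Youden = 0.59 + 0.82 − 1 = 0.41, as stated. At 11.7% incidence:

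- Share flagged = 0.59 × 0.117 + 0.18 × 0.883 = 0.228.
- Positive predictive value = (0.59 × 0.117) / 0.228 = 0.303.

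This agrees with the 30% planning incidence, so the stated operating point and the sample-size assumption are consistent.

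**Threshold on the β scale.** P ≥ 0.13 is equivalent to β ≥ ln(0.13/0.87) = −1.901.

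**The equation as printed.** β = −14.2334 + 0.0681·age + 0.5005·TG + 2.8165·FPG + 1.6925·HbA1c, where TG is triglycerides and FPG is fasting glucose, both in mmol/L, and HbA1c is in %.

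| Assumed profile (age, TG, FPG, HbA1c) | Sum of terms | β | P | FPG needed for P = 0.13 |
|---|---|---|---|---|
| Ordinary: 30, 1.3, 4.6, 5.2 | 2.043 + 0.651 + 12.956 + 8.801 | 10.217 | 0.99996 | 0.30 |
| Very low: 20, 0.5, 3.5, 4.5 | 1.362 + 0.250 + 9.858 + 7.616 | 4.853 | 0.992 | 1.10 |
| Extreme low: 18, 0.3, 3.0, 4.0 | 1.226 + 0.150 + 8.450 + 6.770 | 2.362 | 0.914 | 1.49 |

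The extreme low profile still scores about seven times the threshold (0.914/0.13 = 7.0).

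**Simulation.** One million women with no binary risk factor were drawn under each of three assumed distributions, with mean glucose/HbA1c of 4.5/5.0, 4.3/4.9 and 4.0/4.7. Every woman scored at least 0.13 in all three. The lowest single scores were 0.964, 0.785 and 0.201. As printed, sensitivity is about 100%, specificity about 0% and Youden about 0.

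**Simple misreadings tested** on a 30-year-old with TG 1.2, glucose 4.5 and HbA1c 5.0 (P = 0.99993 as printed):

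- HbA1c as a fraction: P = 0.76.
- Glucose or triglycerides in mg/dL, or HbA1c in mmol/mol: β between 54 and 225.
- Sign of β reversed: P = 0.00007, and 0.008 for the very low profile, so the ordinary woman ranks below the low-risk one.
- Intercept lower by 10: P = 0.39.

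None of these restores a usable rule. For scale only, and not as a correction: the ordinary profile in the table would sit at 0.13 with an intercept near −26.4, about 12 units below the printed one.

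**Consequence if everyone qualifies.** Power for a 30% relative reduction, two-sided 5%, with 225 per group (half of the 450 expected to complete):

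| Control incidence | Intervention incidence | Power |
|---|---|---|
| 4.5% | 3.15% | 11% |
| 11.7% | 8.19% | 24% |
| 25.1% | 17.57% | 50% |
| 30% (plan) | 21% | 59% |

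The last row is the comparator for this point. That it lies below the planned 80% is a separate sample-size matter and adds no weight here.

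**The case against.** The strongest reply is that the printed equation need not be the one in use. Background says the model was developed and published earlier, and Participant timeline says staff screen with the model, not with the article's text. The 30% planning incidence is attributed to the group's own data on flagged women and agrees with the stated 59%/82%. This suggests that a working model exists and that the article contains a misprint. The formula also has an unclosed bracket and a stray full stop, so a term or scaling could have been lost in typesetting. **This stands as a limit on the consequences:** the article does not show that enrichment has failed. It does not rescue the equation, because the numbers and units look intact and no visible gap accounts for some 12 units of β.

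The operating point is also cited to a different reference from the one Background gives for the group's model, so its source is unclear. The eligibility rule fails as printed wherever those figures come from.

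The 11.7% is an East Asian figure, not the three centres' own rate. That is fair, and it is why the power loss is given as a range. A reader might also recover the right equation from the earlier publication, which cannot be checked from the article.

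**Conclusion.** The concern holds. As printed, with the stated units and link, the equation gives every plausible first-trimester profile a probability above 0.13, usually close to 1. Specificity is about 0% against the stated 82%. The covariate values are assumed, but the conclusion is not sensitive to them: even an 18-year-old with triglycerides of 0.5 mmol/L and HbA1c of 4.0% would need a fasting glucose below 1.45 mmol/L to be screened out.

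The article cannot show which term is wrong or what the centres' calculator contains. The unselected cohort and the fall in power to about 24% (11% to 50%) are therefore conditional on two things: the printed version being used for screening, and incidence in unselected women lying within the range in Background. The failure of the published eligibility rule is not conditional on either. It must be corrected, because it defines the trial population.

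**What to change.** 1. Compare the printed intercept, coefficients, units and any centring or scaling with the fitted model and with the calculator used at each of the three centres. The sponsor holds the source, and no replacement value can be inferred from the article.
2. Publish the corrected equation with two worked examples, one below 0.13 and one above, and correct the citation for the operating point if it is wrong.
3. State which version was used for screening. If the printed version was never used, the correction is enough.
4. If any woman was screened with the printed version, re-score all enrolled women from their recorded first-trimester values and flag those whose corrected risk is below 0.13. Add an analysis of the primary outcome in women at or above 0.13, keeping the intention-to-treat analysis of all randomised women. Fix this in writing before anyone sees outcomes by arm. Revisit the 30% planning incidence at the same time.

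The cost is a published correction and, only if step 4 applies, a short re-scoring program on data already collected.

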### Recruitment and randomisation

The research staff will verbally inform eligible pregnant women that the hospital is currently conducting a multicentre clinical trial to identify better preventive strategies for GDM and that they are eligible to participate. If they fully understand and are willing to join the study, they will meet the research staff in person at the hospital, sign an informed consent form and officially participate in the project prior to 14 gestational weeks. Baseline data, including sociodemographic characteristics and medical and maternal history, will be collected by standardised questionnaires. Each participant will be given a sequential study number by research staff. Subsequently, their basic information will be entered into an internet-based and password-protected clinical research management system (ResMan Research Manager, supported by West China Hospital, Sichuan University, China), which will automatically generate a research code and randomly allocate participants to the intervention group or the control group at a ratio of 1:1. The research assistants responsible for data collection, biostatisticians and data analysts will be masked to study group allocation. Given the nature of the intervention, the participants and investigators will be aware of the assignment.

### Dietary intervention

For the intervention group, one-to-one nutritional counselling with the same dietician will be arranged 3 times before the OGTT (13–16 w, 17–20 w, 21–24 w). The average contact time with a dietician will be 30 min for each subject per visit. The primary intention of the nutritional intervention is to promote a long-term healthy dietary pattern and prevent excessive GWG throughout pregnancy, thereby potentially lowering the prevalence of GDM and resulting in better perinatal outcomes. Qualified dieticians from three centres will receive specific training with the aim of establishing a uniform set of intervention standards for the study. The proposed dietary strategies are based primarily on the International Federation of Gynaecology and Obstetrics (FIGO) endorsed guidelines for pregnant women and the Diagnosis and Therapy Guideline for Pregnancy with Diabetes Mellitus (2014) from the Chinese Medical Association (CMA) and Chinese Dietary Guidelines (2016) from the Chinese Nutrition Society [31–33]. Macronutrient intake composition will be recommended to be in compliance with current clinical practice for patients diagnosed with GDM. Protein, fat and carbohydrates should account for 15–20%, 25–30%, and 45–50%, respectively, of the total energy intake. Low-glycaemic index (GI) foods (target GI ≤ 50) are recommended as carbohydrate sources due to their associations with appropriate GWG and ameliorated maternal glucose tolerance [34]. More specifically, the counselling will focus mainly on GWG management, food preparation techniques, meal timing, and proportions of whole grains, dark green leafy vegetables, nuts, fruits and lean protein consumption. Refined carbohydrate foods and other sugar-rich products will be restricted.

Compared with common dietary consultations, the greatest advantage of the intervention in this study lies in self-administered 3-day food records, a valid resource for nutritionists to pinpoint problems precisely and optimise dietary patterns individually. At enrolment, participants will be instructed by a trained research practitioner on how to record their diet diary in detail. A consecutive 3-day food record should cover 2 weekdays and 1 weekend day excluding special occasions (e.g., banquets, business trips, or tours). To obtain information that can represent participants’ usual dietary intakes, they are asked to truthfully record all foods and beverages consumed as accurately as possible. The food diary consists of consumption time, food category, preparation techniques and the accurate amount of raw ingredients in mixed dishes. To ensure a more precise and unified quantification of foods, participants will receive an 18-page colouring booklet that graphically shows commonly consumed local foods with serving sizes and different measurement tools. It is suggested that participants take pictures of foods for which it is difficult to estimate portion sizes themselves, which provides intuitive evidence for objective postcompletion revision by nutritionists. Before each appointment with a dietician, women assigned to the intervention group will be asked to complete a 3-day food record in advance. To ascertain whether their dietary patterns changed after the OGTT, 2 additional diet diaries will be required to be completed at 27–30 and 32–34 gestational weeks. During the study visits, food records will be entered by dieticians into nutritional analysis software (NutriStar Software, Zhending, China) based on the China Food Composition Tables (2018) [35], which will help to calculate energy and nutrient intake for in-depth quantified evaluation. Then, a tailored dietary prescription will be developed as mentioned above for further management in the intervention group. Subsequent visits will be scheduled by dieticians or research staff at the end of each consultation. Strategies have been established for retention of participants enrolled. A specific trained research staff will be responsible for follow-up and direct communications with all the participants at each trial centre. The research staff will not only remind them in person to fill in 3-day food records or to visit a dietician at designated gestational weeks, but also emphasize the benefits of the study to encourage them to complete follow-up. For convenience, study visits will be arranged in parallel with standard antenatal clinic visits. Additionally, priority access to ultrasound examinations during pregnancy will be provided. Adherence to the intervention is anticipated to be assessed comprehensively taking into consideration nutritional clinic attendance as required and the number of qualified 3-day food records. If needed, comparisons between nutrition prescriptions and actual diet records will be performed.
